#### Screening survey

The screening survey will utilise the MoCA-J tool, employed for dementia screening, MCI, assessment, and evaluation of visuospatial and executive functions, naming, memory, attention, recitation, word recall, abstract concepts, delayed replay, and disorientation [32, 33]. The tool is considered reliable and has been previously validated [23]; patients who score < 26 on the MoCA-J are more likely to be diagnosed with MCI. A previous study tested the feasibility of administering the MoCA-J in web format and reported high reliability and satisfaction levels [34]. This study will conduct neuropsychological testing in web format as required.

#### Survey items related to health behaviours

The status of health behaviours related to dementia risk will be assessed by a survey. For each regular exercise (at least thrice a week), dietary modification, social participation, and cognitive training, five behavioural change stages will be assessed using the transtheoretical model [35]. Regarding regular exercise, the options include ‘I do not exercise regularly, and do not intend to exercise in the future (within the next 6 months)’ (precontemplation phase); ‘I do not exercise; however, I intend to start exercising in the future (within the next six months)’ (contemplation); ‘I intend to start exercising now (within a month), and I am preparing for it, or I am exercising regularly (at least three times a week) but not regularly’ (preparation); ‘I have started regular (at least 3 times a week) exercise within the last six months’ (action); and ‘I have been exercising regularly (at least three times a week) for more than six months’ (maintenance).

#### Comprehensive functional assessment

##### (1) Lifestyle

A questionnaire will be used to evaluate items related to dementia risk: exercise habits, sleep, medication and medical history, cognitive activities, social activities, subjective cognitive impairment, hobbies and activities, friendships, eating habits, and disease information.

##### (2) Food intake diversity

The Food Diversity Score, consisting of 11 items, has been adapted [36] to assess participants’ frequency of consuming 13 food items over the past week, including cereals, fish and shellfish, meat, eggs, milk, dairy products, beans, seaweed, potatoes, fruit, and nuts. Each item is scored as 1 (almost every day), 0.5 (once every 2 days), 0.25 (once or twice a week), and 0 (rarely eaten).

##### (3) Social participation

Social engagement evaluation will involve a questionnaire examining participation across eight types of groups [37]: local community, including neighbourhood associations, senior citizen clubs, and fire-fighting teams; hobby groups; sports groups or clubs; politics-related organisations or groups; industry-related or trade associations; religion-related organisations or groups; volunteer groups; and other groups.

##### (4) Frailty-related index

The Simple Frailty Index [38] will be used to evaluate the degree of frailty among older adults. The degree of frailty is assessed using five items (weight loss, walking speed, movement, memory, and fatigue); one point is given for each item that applies. A score of ≥ 3 is considered frail, and a score of 1–2 is considered pre-frail.

##### (5) Health-related quality of life

To evaluate the health-related quality of life, a health index of the EQ-5D will be used. It comprises five dimensions: mobility, self-care, pain/​discomfort, usual activities, and anxiety/depression. The scores on these dimensions are summed, and a single index score (utility) is calculated with reference to previous studies [39].

##### (6) Physical performance

Physical performance will be assessed by measuring the usual gait speed over a distance of 2.4 m on a walkway [40]. Hand grip strength will be measured for both hands using a standard digital hand grip dynamometer (Takei Scientific Instruments Co., Ltd, Japan,) while participants stand with their shoulders adducted and neutrally rotated and the elbows fully extended [41].

### Implementation outcomes

The study will measure implementation outcomes, including participant adherence, fidelity, feasibility, acceptability, appropriateness, and cost—for both programme providers and programme participants [42]. Quantitative and qualitative methods will be used to collect data, depending on the purpose. The primary endpoint is the participant’s adherence at 6 months—the proportion of participants who continue to participate in the adapted multi-domain intervention programme. Fidelity is measured as the degree to which procedures and regulations are followed in the programme implementation. Based on a predesigned checklist of procedures, a score of 100 is given if the intervention provider fulfils all procedures. Additional implementation outcomes will be measured qualitatively using semi-structured interviews. Feasibility will be measured for the implementers at 6 and 12 months to assess whether multi-domain interventions are feasible (e.g. ‘Do the multi-domain interventions seem to be implementable?’). The acceptability of the interventions will be measured for the implementers and participants at 6 and 12 months to assess whether they agree with, prefer, or are satisfied with the programme content (e.g. ‘Do the multi-domain interventions seem appealing to you?’). The appropriateness of the intervention will be measured for implementers at 12 months and participants at 6 and 12 months, to assess whether the programme is appropriate for the site (e.g. ‘Do the multi-domain interventions seem fitting?’). Each of these interview items is based on validated measurements [43]. All interviews will be conducted by researchers trained in qualitative research, using a combination of individual interviews and focus groups. While community-dwelling older adults will participate in qualitative research, not all will undergo individual interviews. These individual interviews will be specifically aimed at gaining deeper insights into qualitative implementation outcomes, especially acceptability and appropriateness. For example, in situations of low acceptability, individual interviews will be particularly valuable. Programme providers will participate in focus group interviews to gain perspectives from group dynamics and interactions. Implementation costs will be determined by prospectively collecting information on time spent by members of the research team from programme development to implementation; costs of supplies and equipment will also be determined.

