### Objectives

This feasibility trial aims to investigate the feasibility of sustained participation in the adapted intervention and collect data for determining the feasibility of proceeding to the subsequent effectiveness study. The primary objective of the trial is to evaluate the proportion of participants continuing engagement in the adapted multi-domain intervention programme. Secondary objectives include (1) evaluating health outcomes, including cognitive function changes, behavioural change indicators, and other lifestyle indicators; (2) evaluating implementation outcomes, such as fidelity, intervention acceptability, appropriateness, and implementation costs; and (3) verifying that the intervention effect of the original J-MINT intervention remains robust or has potentially strengthened compared to the J-MINT control group. Moreover, this study contributes to achieving SDG Goal 3 by exploring the feasibility of a community-based dementia prevention programme, which, if successful, can improve older adults’ health and well-being, reduce the burden of dementia on individuals and their families, and support the promotion of healthy aging in local communities.

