#### Programme structure

During the first six months, the research team will lead the community intervention, followed by local public health nurses for the subsequent six months. The research programme will be conducted once every two weeks (26 times a year), with the local government-implemented exercise programme every other week, resulting in weekly engagement. The research programme will consist of 60 min of exercise and 30 min of group work. The group work will feature content related to dementia prevention (e.g. lifestyle diseases, dietary habits, social participation), and facilitators from the research team and the local government will promote interaction among participants. The specific content of the intervention is explained below.

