### Assessment

Following participant consent, baseline observations and examinations will be conducted. Specific observations and examinations will be carried out after six (± 2) months of participation and at the 12-month mark. The items and participants for each of the health and implementation outcomes are presented in Table 3. Each measure is described in detail.

**Table 3 Tab3:** Outcome measures, informants, and timeframe of assessments

Construct	Measure/indicator	Informant		Timeframe (months)		
		Participants	Providers	0	6	12
Cognitive function	MoCA-J	×		×	×	×
Physical function/status	Gait speed	×		×	×	×
	Grip strength	×		×	×	×
	Body mass index	×		×		×
Awareness of healthy activities	Behavioural modification stages	×		×	×	×
Comprehensive geriatric assessment	Lifestyle	×		×	×	×
	Variation in diet	×		×	×	×
	Social participation	×		×	×	×
	Health-related quality of life	×		×	×	×
	Physical activities	×		×	×	×
Implementation outcomes	Feasibility	×			×	
	Fidelity		×			×
	Participants’ adherence	×			×	
	Acceptability	×	×		×^a^	×^b^
	Appropriateness		×			×
	Cost			×*	×*	×*

*Gather information prospectively; ^a^ obtain from participants; ^b^ obtain from providers

Abbreviations. MoCA-J: The Japanese version of Montreal Cognitive Assessment

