
### Analysis

The primary outcome measures of all participants will be analysed. The proportion of individuals sustaining programme engagement will be calculated from the initial assessment to the six-month follow-up for those attending ≥ 60% of classes (with at least half of the classes attended). The rationale for setting the proportion is based on a study that examined the intervention effects by participants’ adherence level in the FINGER study [7]. The above-mentioned study found that cognitive decline was suppressed when at least 50% of individuals participated and at least 57% of the group attended classes.

For the secondary outcome measures, stratification will be performed for older adults with a risk of dementia (MCI) and those without. The programme adaptation will be evaluated to determine whether the effect of the original intervention has weakened or been maintained compared to the control group in the original study. Specifically, changes before and after the intervention will be analysed for health behaviour and comprehensive functional evaluations. For continuous variables, summary statistics will be calculated for changes in the six-month period from the initial assessment and tested using paired sample t-tests or, for non-parametric data, Wilcoxon’s signed-rank tests. For categorical variables, the frequency and proportion of cases corresponding to each category and 95% confidence interval will be calculated at each time point. The confidence interval will be calculated using the Clopper–Pearson method, which provides an accurate estimation for binomial proportion confidence intervals and is particularly useful when dealing with small sample sizes or extreme proportions [44]. If necessary, changes before and after the intervention will be compared using McNemar’s test, a statistical test used to analyse paired nominal data. It is appropriate for our design as it evaluates changes in two related groups over time [45]. Qualitative data used for implementation outcomes will be analysed by summary content analysis [46, 47]. Specifically, recorded interview data will be transcribed verbatim. Important concepts and themes will be coded for category creation. Coding will be performed by a researcher confirmed by another. The research team will validate categories aggregating similar codes. Qualitative analysis will benefit from consultation with a qualitative research expert.

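### The adherence endpoint and the only stated continuous change analysis stop at month 6, before nurses take the lead, so sustained participation under nurse-led delivery has no scheduled outcome

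*Protocol article*

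**What the plan says.** **Aim.** Under Objectives, the trial sets out to "investigate the feasibility of sustained participation in the adapted intervention" and to gather data for deciding whether to move to an effectiveness study.

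**Who leads, and when.** The Programme structure section divides the year as follows: "During the first six months, the research team will lead the community intervention, followed by local public health nurses for the subsequent six months". According to the Design section, nurses are already part of the delivery team in the first half. It names protocol compliance and fidelity as outcomes for the second.

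**Adherence.** Under Implementation outcomes: "The primary endpoint is the participant’s adherence at 6 months". Under Analysis, the proportion "will be calculated from the initial assessment to the six-month follow-up for those attending ≥ 60% of classes". In Table 3 (Assessment), the row "Participants’ adherence" is marked at month 6 only.

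**Health outcomes.** Table 3 schedules the MoCA-J, gait speed, grip strength, behavioural stages and the geriatric assessment items at 0, 6 and 12 months. The row "Body mass index" is marked at 0 and 12 only. For continuous variables, Analysis says that "summary statistics will be calculated for changes in the six-month period from the initial assessment", tested by paired t-test or Wilcoxon signed-rank test. For categorical variables, frequencies and proportions are reported and a "95% confidence interval will be calculated at each time point". McNemar's test, and a general sentence on change before and after the intervention, name no month.

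**Other month-12 outcomes.** Table 3 places fidelity, appropriateness and provider acceptability at month 12. The Implementation outcomes text also has implementers' feasibility interviews, and participants' acceptability and appropriateness interviews, at both 6 and 12 months.

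**The concern.** The trial asks whether people keep taking part in a programme adapted so that a municipality can run it. Leadership passes to municipal nurses at the mid-point, yet the outcome that measures taking part is fixed at that same point. Three places agree on month 6 (the endpoint definition, the analysis window and Table 3), so this is a design decision and not a slip in one table.

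The Discussion expects confirmed feasibility to open the way to wide community use and to a hybrid effectiveness–implementation study. If attendance fell away after the handover, the primary result would not change, and no other scheduled outcome counts attendance in months 7–12.

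The health outcomes have a smaller version of the same gap. Participants are measured again at month 12, but the stated change analysis for continuous variables stops at month 6, and one listed measure has no month-6 value to analyse.

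**Working it through.** **Inputs.** 60 participants, as 30 in each of two communities (Participants). 26 research sessions a year, one every two weeks (Programme structure). Adherence threshold of at least 60% of classes, over baseline to month 6 (Analysis). The enrolment figure reproduces: 2 × 30 = 60. No formal sample size calculation was made, and the point does not depend on one.

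**Step 1: sessions in each half.** Assuming even spacing, 26 / 2 = 13 sessions before the handover and 13 after.

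**Step 2: what the month-6 rule requires.** 0.60 × 13 = 7.8, so 8 sessions; 8/13 = 61.5%.

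**Step 3: what the rule allows over the year.**

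| Sessions 1–13 | Sessions 14–26 | Adherent on the primary endpoint? | Attendance over the year |
|---|---|---|---|
| 8 | 0 | Yes (61.5%) | 8/26 = 30.8% |
| 13 | 0 | Yes (100%) | 13/26 = 50.0% |

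Applied to the full year, the same rule needs 0.60 × 26 = 15.6, so 16 sessions. Nobody who stops at the handover can reach 16, yet anyone with 8 or more by then is counted as adherent.

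**Step 4: does it matter which classes count?** If the alternate-week municipal classes are included, there are 52 a year and 26 per half. The rule then needs 16 of 26 (61.5%), and stopping at the handover gives 16/52 = 30.8%. The result is the same.

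**Step 5: does the visit window help?** The month-6 examinations have a window of ±2 months. At 26 sessions a year, month 4 corresponds to 26 × 4/12 = 8.7 sessions and month 8 to 26 × 8/12 = 17.3. If the window also governed the adherence count, a late visit could take in a few nurse-led sessions and an early one could miss some research-led ones. Neither amounts to an assessment of the second half.

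**Step 6: precision of an added outcome.** With all 60 in the denominator, the 95% Clopper–Pearson interval would be 67.7% to 89.2% for an assumed 48/60 (80%), and 56.8% to 81.2% for an assumed 42/60 (70%). These proportions are illustrations. The intervals are as precise as the primary result would be at the same proportions, so no larger sample is needed.

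**Step 7: health outcomes, schedule against stated analysis.**

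| Outcome | Measured at (months) | Stated analysis | Reaches month 12? |
|---|---|---|---|
| MoCA-J, gait speed, grip strength and other continuous measures | 0, 6, 12 | Change from 0 to 6 | No |
| Body mass index | 0, 12 | Change from 0 to 6 | Cannot be computed |
| Categorical measures | 0, 6, 12 | Proportion with interval at each time point; McNemar's test if needed | Yes |

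**The case against.** The strongest reply is that a 6-month primary endpoint is a legitimate and explicit choice in a feasibility study, and that the second half is meant to be judged by other outcomes. Much of this stands. Fidelity, appropriateness, acceptability and implementers' feasibility are assessed at 12 months, and categorical outcomes are summarised there. A reader might infer that every change analysis ends at month 6, or that health is never assessed in the nurse-led half. The documents do not support either reading: McNemar's test and the before-and-after sentence are not tied to month 6, and most health measures are taken at month 12.

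It is also fair that the first half is not purely a researchers' class. Nurses and instructors share delivery, the Abstract describes a gradual shift of management, and the setting is a community centre from the start. Leadership nevertheless changes only at the mid-point.

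It may be said that fixing the time of the primary endpoint does not rule out recording attendance later, and that Table 3 is imperfect evidence because it disagrees with the text on who is asked about feasibility and when. That is true, but the text offers no later adherence outcome either. The Design section's reference to protocol compliance in the second half could be read as participant compliance, but no measure or time point is attached to it.

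A further inference would be that the trial ought to estimate the effect of the handover. No objective asks for this, and a single-arm comparison of halves is confounded with elapsed time. Nor does the article give a continuation rate after the handover. The 80% continuation figure is from the earlier J-MINT study and is not said to use the 60% attendance rule, so any forecast of the loss would be an assumption.

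On body mass index, the before-and-after sentence covers health behaviour and functional evaluations, and Table 3 lists the measure under physical function and status. The mismatch is minor, but as written the continuous-variable rule cannot be run for it.

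**Conclusion.** The point holds for two things: participant adherence, and the stated change analysis for continuous outcomes. Both stop at month 6, before nurses lead. A positive primary result would support participation in the jointly delivered, research-led half. It could not show that participation was sustained under nurse-led delivery.

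The size is a property of the rule and not a forecast: a participant can count as adherent with 31% attendance over the year, and even perfect first-half attendance followed by none gives 50%, below the trial's own 60%. This assumes evenly spaced sessions and uses the 60% threshold. How many participants would behave this way cannot be known from the article.

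The continuous-outcome part is a gap between schedule and analysis. A separate analysis plan, not shown, might specify 12-month change, but that would not alter Table 3's month-6-only marking for adherence.

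**What to change.** 1. Keep the 6-month primary endpoint as it is.
2. Add two named secondary outcomes: the same attendance rule applied to months 7–12, and to all 26 sessions. Use all enrolled participants as the denominator and Clopper–Pearson intervals, as already planned for proportions. Mark adherence at month 12 in Table 3.
3. Base any statement about nurse-led delivery on these outcomes. Present any difference between halves as descriptive, because leadership changes together with elapsed time.
4. Add 0–12 month change to the continuous analyses, including body mass index. The paired tests already named are sufficient; a mixed model over the three visits is optional.
5. If practicable, complete the existing fidelity checklist in the first half as well.

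**Cost.** Attendance must be recorded through month 12, which the article does not expressly say is planned. There is a little more analysis and, if item 5 is adopted, some extra checklist work. No additional participants or visits are needed.

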
### Analysis

The primary outcome measures of all participants will be analysed. The proportion of individuals sustaining programme engagement will be calculated from the initial assessment to the six-month follow-up for those attending ≥ 60% of classes (with at least half of the classes attended). The rationale for setting the proportion is based on a study that examined the intervention effects by participants’ adherence level in the FINGER study [7]. The above-mentioned study found that cognitive decline was suppressed when at least 50% of individuals participated and at least 57% of the group attended classes.

For the secondary outcome measures, stratification will be performed for older adults with a risk of dementia (MCI) and those without. The programme adaptation will be evaluated to determine whether the effect of the original intervention has weakened or been maintained compared to the control group in the original study. Specifically, changes before and after the intervention will be analysed for health behaviour and comprehensive functional evaluations. For continuous variables, summary statistics will be calculated for changes in the six-month period from the initial assessment and tested using paired sample t-tests or, for non-parametric data, Wilcoxon’s signed-rank tests. For categorical variables, the frequency and proportion of cases corresponding to each category and 95% confidence interval will be calculated at each time point. The confidence interval will be calculated using the Clopper–Pearson method, which provides an accurate estimation for binomial proportion confidence intervals and is particularly useful when dealing with small sample sizes or extreme proportions [44]. If necessary, changes before and after the intervention will be compared using McNemar’s test, a statistical test used to analyse paired nominal data. It is appropriate for our design as it evaluates changes in two related groups over time [45]. Qualitative data used for implementation outcomes will be analysed by summary content analysis [46, 47]. Specifically, recorded interview data will be transcribed verbatim. Important concepts and themes will be coded for category creation. Coding will be performed by a researcher confirmed by another. The research team will validate categories aggregating similar codes. Qualitative analysis will benefit from consultation with a qualitative research expert.

